### 2.9. Outcome Measures

As primary outcome measure, we will consider the effects on pain perception measured on the VAS for the treatment based on the enfacement illusion compared to the control conditions across the visual-exposure sessions.

Secondary outcome measures will include:(a)The evaluation of the effects on the perception of one’s own body image and on the affective and emotional state of the treatment based on the enfacement illusion with respect to the control conditions as evaluated with the BIQ and the PANAS at the beginning and at the end of each visual exposure condition;(b)The assessment of the virtual reality experience within each treatment condition by comparing the embodiment questionnaire (for the experimental group) and the immersive questionnaire (for the control group) across the three visual exposure sessions;(c)The evaluation of the relationship between the affective and emotional state of patients and the change in the perception of pain and one’s body image as assessed via the BSS, the HADS, the ERQ, and the DERS at T0 and T1 in the two visual exposure conditions (experimental group vs. control group).

### 2.10. Data Collection

Psychologists conducting evaluations will receive appropriate instruction and guidance regarding all of the outcome parameters and assessments that will be taken. The research staff collecting the data will be blinded to the group allocation.

### 2.11. Data Management

Study data will be recorded in a repository in an Excel file. All participants will be registered with an identification code in a random order. The repository will be kept updated to reflect the subject’s status at each stage during the course of the study. The collected data, after scientific publication, will be shared in public repositories (Zenodo) according to the good practice of data sharing.

### 2.12. Statistical Analysis

#### 2.12.1. Sample Size Calculation

According to the main goal of demonstrating possible changes in pain perception—as assessed on the VAS scale—in patients with CM after a non-pharmacological intervention, the number of participants needed is 100. This number was calculated in order to guarantee a statistical power of 80% and a statistical level of 95% for a one-tailed *t*-test in order to detect an effect size (d) = 0.5 by expecting significant differences between the two groups in terms of changes in pain perception both after each treatment session and at the end of the entire intervention in favor of patients who fall into the experimental group (delta pain for the experimental group = −40 ± 100; delta pain for the control group = 10 ± 100). With the above data, the required sample size necessary to detect significant differences is 50 subjects per group. Extra participants will be recruited in case of dropouts.

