## 2. Materials and Methods

### 2.1. Study Design

The proposed study is a prospective double-blind RCT with two arms. A CONSORT flow chart for enrollment and randomization is shown in Figure 1. Patients fulfilling inclusion criteria, once they have signed the informed consent form, will undergo a baseline assessment (T0) using the below-listed tests and will be randomized to one of two groups: experimental and control. Both groups will be exposed to three VR sessions each lasting approximately 20 min during a one-week period. The first session will be carried out immediately after enrollment and T0, whereas the next two will be carried out in the following days when the patients will report to have a migraine attack. At T0 and at the end of the intervention (T1), the patients will fill in a questionnaire based on behavioral measures related to their emotional and psychological state and their body image perception. T1 assessment will then be carried out at the end of the last VR session. Before and after each VR session the level of pain, body image, and affective state of the patients will be assessed. Furthermore, after each VR session, the sense of embodiment (experimental group) or the sense of immersiveness (control group) will be assessed.

This study protocol conforms to the Standard Protocol Items: Recommendations for Interventional Trials (SPIRIT) guidelines (see Supplementary Table S1).

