### 2.8. Visual-Exposure Conditions

Each VR session will be conducted by the same experimenter (i.e., a psychologist) in order to avoid any related effects. Both visual exposure conditions will be conducted with the participant seated in a chair. In case of cyber sickness, participants will be free to discontinue the VR exposure at any moment.

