#### 2.12.2. Planned Analysis

Statistical analysis on outcome measures will be conducted using Stata 13 (StataCorp LP, College Station, TX, USA). The data collected will be first analyzed using descriptive statistical techniques. As the primary outcome, differences in terms of VAS scores at session 1 pre assessment and session 3 post assessment in the two groups will be evaluated using ANOVA-one factor (factor: groups) (or the Kruskal–Wallis test, after a normality analysis). Finally, mixed-effects models will be implemented to examine the longitudinal aspect of the study that represent changes across the visual-exposure sessions. For secondary outcomes concerning the changes in the perception of one’s own body image and on the affective and emotional state as well as the assessment of the VR experience, the analysis plan will be similar to the one planned for the primary outcome. Regarding the evaluation of the relationship between the affective and emotional state of the patients and the change in the perception of pain and one’s body image, a correlation analysis will be performed between the considered scales. For all outcome analyses, an intention-to-treat (ITT) approach will be used, according to CONSORT guidelines [78,79]. An alpha level ≤0.05 will be considered as significant.

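### The primary ANOVA can use only randomised patients who reach session 3, and recruiting extra participants for dropouts does not deliver the declared intention-to-treat analysis

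*Protocol article*

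**What the plan says.** Five statements in the protocol article bear on this point.

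- **Primary test (Section 2.12.2).** VAS at the session 1 pre assessment and the session 3 post assessment is compared between groups by one-factor ANOVA, or by Kruskal–Wallis if normality fails. Mixed-effects models across the sessions follow, as a further analysis of the longitudinal aspect.
- **When sessions happen (Section 2.1).** Session 1 follows enrolment and T0 directly. Sessions 2 and 3 come on later days, "when the patients will report to have a migraine attack", and all three fall in one week.
- **Where VAS is recorded (Table 1).** Before and after each session only. None is scheduled at T0 or T1.
- **Handling of loss (Section 2.12.1).** "Extra participants will be recruited in case of dropouts". No dropout rate, inflation or fixed randomised total is given.
- **Analysis population (Section 2.12.2).** "For all outcome analyses, an intention-to-treat (ITT) approach will be used".

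Section 2.5 places randomisation after T0, and Section 2.1 places session 1 directly after T0. Anyone who misses session 3 has therefore already been randomised.

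**The concern.** An ANOVA or Kruskal–Wallis test on a contrast that ends at session 3 post needs that value from every patient it includes. A patient who reports no attack on enough of the remaining days has no such value, even if she never withdraws. Whether she reports an attack is close to what the trial measures, because a patient whose headaches ease is less likely to be called back. The patients left in the test may then differ from those randomised.

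Extra recruitment answers a different question, namely how many values the test has. It leaves unchanged which randomised patients are missing from it. At stake is whether the headline comparison is between the groups as randomised or between those in each group who went on to have session 3. If missingness depends on pain and works differently in the two arms, the pain contrast is biased, and a topped-up sample makes the loss harder to see.

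**Working it through.** **1. The plan's own sample size.** Inputs from Section 2.12.1: "a statistical power of 80% and a statistical level of 95% for a one-tailed" t-test, "in order to detect an effect size (d) = 0.5", and "delta pain for the experimental group = −40 ± 100; delta pain for the control group = 10 ± 100". The difference is 10 − (−40) = 50, so d = 50/100 = 0.5. By the normal formula,

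n per arm = 2(z₀.₉₅ + z₀.₈₀)²/d² = 2(1.645 + 0.842)²/0.25 ≈ 49.5, rounded up to 50.

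This reproduces the stated figure: "the required sample size necessary to detect significant differences is 50 subjects per group". Power at 50 per arm is 0.804 by the normal formula and 0.799 by the exact t calculation. The number is right on its own inputs and holds no reserve for loss.

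**2. Who can enter the primary test.**

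| Patient | VAS available (Table 1) | In the ANOVA as stated? |
|---|---|---|
| Sessions 1, 2 and 3 | six ratings | yes |
| Sessions 1 and 2 only | four ratings | no, unless session 3 is imputed |
| Session 1 only | two ratings | no, unless session 3 is imputed |

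All three rows are randomised patients. An extra recruit who completes adds to the first row and moves nobody out of the other two.

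**3. When this biases the contrast.** In one arm, let m be the share without session 3, and Δ the mean pain change they would have shown minus the mean change of those observed. The full-arm mean is the observed mean + mΔ. The error in the observed group contrast (experimental minus control) is therefore

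m_C Δ_C − m_E Δ_E.

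It is zero if the two products are equal. Recruiting more patients who are lost in the same way changes neither m nor Δ, so it does not reduce the error. The document gives no value for either quantity, so the size and direction of the bias cannot be computed.

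**4. How many might miss session 3 (illustration).** The protocol gives no rate. Assumptions: each following day is a headache day with independent probability p, and two such days are needed for sessions 2 and 3. The Introduction defines chronic migraine as 15 or more days a month, so p = 15/30 = 0.5 is the lower limit; p = 20/30 = 2/3 is a more frequent case, chosen for comparison. One week leaves 6 days after session 1; 5 allows for one unusable day.

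P(fewer than 2 of k days) = (1 − p)ᵏ + k·p·(1 − p)ᵏ⁻¹

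| | k = 6 | k = 5 |
|---|---|---|
| p = 1/2 | (1 + 6)/64 = 10.9% | (1 + 5)/32 = 18.8% |
| p = 2/3 | (1 + 12)/729 = 1.8% | (1 + 10)/243 = 4.5% |

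Real headache days cluster, so these figures are rough. They cover only the absence of a headache day, not withdrawal or a visit that could not be arranged.

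**The case against.** The strongest reply is that nothing in the article excludes anyone. It does not say that dropouts leave the analysis, that a recruit takes a dropout's place, or that 50 completers per group will be analysed. Over-recruitment is compatible with intention to treat if all randomised patients are kept, and a rule for missing values may sit in a full protocol or SAP that is not shown. This stands against a stronger reading. A reader might infer that the declared intention-to-treat analysis is a completer analysis under another name, and the text does not establish that. It does not remove the narrower point, which rests on what is stated: a test that needs session 3, a session that depends on an attack, and no VAS elsewhere.

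Other parts of the reply also stand:

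- Mixed-effects models are planned and can use patients with one or two sessions. They are, however, listed after the ANOVA and not as the primary test.
- A reader might infer that session 3 requires two further attacks. The text requires only that an attack be reported on the days concerned, and one long attack might serve both sessions.
- Section 2.8 says that "participants will be free to discontinue the VR exposure at any moment". Stopping an exposure is not withdrawal from assessment, and such a patient can still rate her pain. Section 2.13 separately allows leaving the study.
- Differential loss by arm is possible, since the arms differ in content, but nothing in the document shows it.
- One could also argue from reduced power. That would assume losses are not made up, whereas the protocol intends to make them up. The issue is who is in the test, not how many.

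**Conclusion.** The point holds in a limited form. As stated, the primary ANOVA or Kruskal–Wallis test can include only randomised patients who reach session 3. Reaching it depends on reporting an attack, so missing values can be related to pain, and extra recruits do not bring the missing patients in. The declared intention-to-treat analysis is therefore not delivered by the primary test plus extra recruitment.

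The share affected is unknown. The illustration gives about 11% to 19% at the minimum headache frequency and about 2% to 5% at 20 days a month. It rests on independent days and on two headache days being enough. In this population most patients would probably reach session 3. The sample size of 50 per group is not in error on its own inputs.

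**What to change.** 1. Make the mixed-effects model already planned the primary analysis: likelihood-based, on all available VAS ratings, with the group contrast at session 3 post as the estimate. Session 1 directly follows enrolment and T0, so nearly every randomised patient should contribute at least those ratings.
2. State that every randomised patient stays in the allocated arm, and that extra recruits are added to the randomised patients and do not replace them.
3. Add a delta-adjusted sensitivity analysis that shifts the missing session 3 values by a range of amounts, separately by arm.
4. Report missed sessions by arm and reason (no attack reported, cyber sickness, other).

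The cost is some wording, one sensitivity analysis and a little more analysis work. The model relies on values being missing at random given the observed ratings, which cannot be verified; item 3 probes it. Simply inflating the randomised total, for example to 100/(1 − 0.10) = 111.1, or 112 for equal arms, at an assumed 10% loss, would restore the number of patients with session 3 but would not remove the selection.

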#### 2.12.2. Planned Analysis

Statistical analysis on outcome measures will be conducted using Stata 13 (StataCorp LP, College Station, TX, USA). The data collected will be first analyzed using descriptive statistical techniques. As the primary outcome, differences in terms of VAS scores at session 1 pre assessment and session 3 post assessment in the two groups will be evaluated using ANOVA-one factor (factor: groups) (or the Kruskal–Wallis test, after a normality analysis). Finally, mixed-effects models will be implemented to examine the longitudinal aspect of the study that represent changes across the visual-exposure sessions. For secondary outcomes concerning the changes in the perception of one’s own body image and on the affective and emotional state as well as the assessment of the VR experience, the analysis plan will be similar to the one planned for the primary outcome. Regarding the evaluation of the relationship between the affective and emotional state of the patients and the change in the perception of pain and one’s body image, a correlation analysis will be performed between the considered scales. For all outcome analyses, an intention-to-treat (ITT) approach will be used, according to CONSORT guidelines [78,79]. An alpha level ≤0.05 will be considered as significant.

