### 2.3. Participant Recruitment and Eligibility Criteria

Participants will be recruited among patients referred to the Center. An expert neurologist will verify the eligibility criteria during the recruitment process based on the participants’ history, headache diaries, and neurological evaluation.

Inclusion criteria for patients will be: (a) 18–65 years of age; (b) female sex; (c) fulfilment of the ICHD-3 criteria [2] for CM (with or without medication overuse); (d) previous history of migraine as primary headache; (e) an intensity of migraine attacks between 20 and 80 on a 0–100 VAS. Only females will be included in this study because of the reported differences on pain perception between males and females [70].

Exclusion criteria will be: (a) epilepsy, psychosis, intellectual disability, pregnant women and breastfeeding women; (b) visual problems; (c) presence of chronic non-cephalic pain.

All patients will receive the advice to avoid any abortive medication during the study period. Preventive treatments will be allowed given that they are not expected to affect the outcome of this study.

In order to achieve adequate participant enrolment to reach the target sample size (see Section 2.12.1), we will provide notice of this study among patients referred to our clinic as well as in local newspapers.

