### 2.4. Participant Evaluation

All patients will undergo the following assessment measures, as reported in Table 1, performed by a psychologist, who will be also be responsible for obtaining the informed consent form.

At T0 and T1, the participants will fill in a series of psychological questionnaires as with regards their affective and emotional state:(a)Body Satisfaction Scale (BSS) [71] designed to measure satisfaction/dissatisfaction with 16 body parts;(b)Hospital Anxiety and Depression Scale (HADS) [72] for anxious and depressive symptomatology;(c)Emotive Regulation Questionnaire (ERQ) [73], which is a self-report measure of two emotion regulation strategies (i.e., cognitive reappraisal and expressive suppression);(d)Difficulties in Emotion Regulation Scale (DERS) [74] measuring emotion regulation problems.

Moreover, within each of the three sessions, they will be also evaluated before and after the visual exposure (six times) with the following measures:(a)Pain Visual Analogue Scale (VAS) for pain level on a 0 to 100 scale;(b)Body Image Questionnaire (BIQ) [75] for body image perception;(c)Positive and Negative Affect Schedule (PANAS) [76] for the positive and negative affective state.

Finally, after each visual exposure session, for a total of three times, the patients of the experimental group will fill in a questionnaire (i.e., embodiment questionnaire) related to the level of sense of belonging to the virtual body and the experience of illusion of enfacement [77]. The control group will fill in a questionnaire (i.e., immersive questionnaire) assessing the level of immersion in the virtual environment [39]. This is in order to assess the subjective strength of the two conditions to which patients will be exposed.

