### 2.5. Randomization, Stratification, and Allocation

After T0, random numbers will be generated from a uniform distribution in the range 0–1, dividing the range in two equal intervals and assigning each patient to the group corresponding to the sampled number (1:1 ratio). Allocation of participants will be performed by an independent data manager, who will be not involved in the data collection/analysis.

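### The primary ANOVA has group as its only term, so session 1 pre VAS is not a covariate, and a normality check on the outcome may replace it with a rank test

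*Protocol article*

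**What the plan says.** Section 2.12.2 (Planned Analysis) says that "differences in terms of VAS scores at session 1 pre assessment and session 3 post assessment in the two groups" will be compared by "ANOVA-one factor (factor: groups"), with an alternative in brackets: "or the Kruskal–Wallis test, after a normality analysis". No covariate is named, and neither is the normality test, its threshold or the variable it is applied to. The section then adds that "mixed-effects models will be implemented to examine the longitudinal aspect of the study", without giving model terms. The secondary outcomes on body image, affective state and the VR experience are to be analysed in a similar way.

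Three other places bear on this:
- Section 2.4 and Table 1: pain VAS is recorded pre and post at each session ("they will be also evaluated before and after the visual exposure (six times"), so session 1 pre VAS should exist for every patient.
- Section 2.3: entry requires "an intensity of migraine attacks between 20 and 80 on a 0–100 VAS", so baseline pain can vary widely.
- Section 2.5: allocation is simple randomization, by "dividing the range in two equal intervals and assigning each patient to the group corresponding to the sampled number".

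Section 2.12.1 sizes the trial on the mean change in pain in each group. The likely reading of 2.12.2 is therefore a one-factor ANOVA of the change from session 1 pre to session 3 post. The wording would also allow two separate comparisons, one at each time point.

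**The concern.** On the change-score reading, baseline enters only by subtraction. That fixes its coefficient at 1, whatever the actual relation between baseline and end value. Section 2.1 places session 1 right after enrollment and the later sessions on days with a reported attack, so the two values come from different days and often from different attacks. If they correlate only moderately, subtraction adds noise that a fitted coefficient would avoid. Simple randomization without stratification also leaves chance differences in baseline VAS, which a change score over-corrects when the true slope is below 1.

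The second matter is the switch. If the outcome data decide between ANOVA and Kruskal–Wallis, they also decide whether the primary result concerns a mean difference in VAS points or a shift in ranks. Only the mean difference matches the quantity used for sizing.

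At stake are precision that costs nothing to obtain and a primary hypothesis and effect measure that are fixed before the data are seen.

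**Working it through.** **1. The plan's own figure.** Inputs from 2.12.1: mean changes −40 and 10 (difference 50), SD 100, so d = 0.5; one-tailed test, alpha 0.05 (reading the 95% statistical level that way), power 80%.

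n per arm = 2(1.645 + 0.842)² / 0.5² = 49.5, rounded up to 50. An exact t calculation gives 50.15. The stated 50 per group is reproduced for an unadjusted change score.

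**2. Variance of ANCOVA against the change score.** Let the pre SD be s, the post SD be ks, and the pre–post correlation be r. Per patient:
- change score: s²(1 + k² − 2rk)
- ANCOVA: s²k²(1 − r²)

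The share of variance saved is 1 − k²(1 − r²)/(1 + k² − 2rk) = (1 − rk)²/(1 + k² − 2rk). This is never negative, so in large samples ANCOVA is at least as precise. The two tie when rk = 1.

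The documents give neither r nor k, so both are assumed. With k = 1 the ANCOVA/change ratio reduces to (1 + r)/2.

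| r (assumed) | saved, k = 1 | saved, k = 1.5 |
|---|---|---|
| 0.3 | 1 − 0.65 = 35% | 0.55²/2.35 = 13% |
| 0.5 | 1 − 0.75 = 25% | 0.25²/1.75 = 4% |
| 0.7 | 1 − 0.85 = 15% | 0.05²/1.15 = 0.2% |

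**3. What that means in patients.** With k = 1 and the plan's one-tailed inputs, ANCOVA needs 33, 38 or 43 per arm at r = 0.3, 0.5 or 0.7, against 50. At 50 per arm its one-tailed power is 0.93, 0.89 or 0.86, against 0.80. These figures illustrate only: they inherit the stated SD of 100, which is implausible on a 0–100 scale. The ratios in step 2 do not use that SD.

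**4. Chance imbalance.** At 50 per arm the difference in mean baseline VAS has standard error √(2/50) = 0.2 SD. With k = 1, an imbalance of that size moves the expected change-score difference by (1 − r) × 0.2 SD, which is 0.10 SD at r = 0.5. At r = 0.5 and k = 1 the change SD equals the VAS SD, so this compares directly with the target d of 0.5. ANCOVA removes it.

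**5. The normality switch.** Simulation of 8,000 trials per scenario, 50 per arm, Shapiro–Wilk on residuals at 5% (an assumed rule, since the article names none):

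| scenario | sent to Kruskal–Wallis | tests disagree on significance | rejection rate: ANOVA / Kruskal–Wallis / two-stage |
|---|---|---|---|
| normal, no effect | 5% | 2% | 0.048 / 0.044 / 0.048 |
| normal, d = 0.5 | 5% | 6% | 0.694 / 0.678 / 0.696 |
| VAS clipped at the scale ends, no effect | 94% | 2% | 0.050 / 0.049 / 0.051 |

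Type I error stays near 5% throughout, including for plain ANOVA on the clipped data. The shape of the data does decide which test, and so which effect measure, is primary.

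**The case against.** The strongest reply is that nothing here is an error. Change score and ANCOVA both estimate the treatment effect without bias under randomization, and the trial was sized on change, so analysis and sizing agree. That stands: the point is one of efficiency and pre-specification, not validity.

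The reply also limits the size of the gain. The correlation is not in the documents; a weak one is plausible from the design but not established. The 35%, 25% and 15% also need equal variances. Since entry restricts attack intensity to 20–80 while later scores can use the whole scale, a larger post SD is possible, and the gain can then vanish.

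A third reply is that covariates, model terms and the details of the normality test belong in an analysis plan that is not shown, and that mixed models are planned anyway. This stands only in part. The article does not leave the primary test open: it names a group-only ANOVA and a data-dependent fallback. The mixed models come after it, to describe change across sessions.

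A reader might also infer three stronger points that the documents do not support:
- *Baseline VAS is ignored or wasted.* The sentence names session 1 pre VAS and the sizing uses change, so baseline probably enters by subtraction.
- *The missing covariate cuts power to 70%.* A two-group F-test is two-sided and has power of about 0.70 at 50 per arm and d = 0.5. That shortfall comes from sizing on a one-tailed test, a separate matter.
- *The switch inflates type I error.* The simulated rates of 0.048 and 0.051 show no such effect.

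**Conclusion.** The point holds as an improvement that needs no new data. The primary ANOVA omits an available baseline covariate, and its form is left to a normality check on the outcome. Adding session 1 pre VAS as a covariate cannot lose precision in large samples and removes the effect of chance baseline imbalance. The gain in variance runs from 35% down to 15% for r from 0.3 to 0.7 with equal pre and post variances, and from 13% down to about nil if the post SD is 1.5 times the pre SD. Both r and the SD ratio are assumptions, and the change-score reading of 2.12.2 is the likely one rather than the only one. The cost of the switch is confined to a primary hypothesis and effect measure that depend on the data, with Kruskal–Wallis comparing ranks where the sizing uses mean change.

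**What to change.** In section 2.12.2:
- Name one primary analysis: session 3 post VAS regressed on arm with session 1 pre VAS as covariate, or the equivalent baseline-adjusted contrast at session 3 post from the mixed model. Naming both assessments also settles whether change or separate time points are tested.
- Report the adjusted difference in VAS points with its 95% CI.
- Delete the normality-triggered switch and keep a rank test as a sensitivity analysis.
- Apply the same rule to BIQ and PANAS, which are also measured before and after each session.

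The cost is about two sentences of text. No new data, visits or patients are needed.
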